##### Pre-inclusion criteria (V0)

To be pre-included, patients will have to:

- be aged 18 years or older (male or female),

- be affiliated to a public health system,

- be diagnosed as having had type 1 or 2 diabetes for at least one year before V0,

- have a last known value of HbA1c, measured within three months prior V0, between 6.8% and 9.7%,

- have received stable antidiabetic therapy (no changes to diet, medication, dosage or formulation) during the three months preceding V0,

- have at least six natural permanent teeth,

- be available for all study visits over three months in the Dental Care Departments (V1 to V6),

- be able to give their written informed consent.

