### Study assessments

#### Periodontal status

A full-mouth periodontal examination will be performed by trained dentists-examiners at V1 and V4 for both groups. The clinical examination will include depth of periodontal pockets (PPD in mm), level of clinical attachment (CAL in mm) and bleeding on probing (BOP: yes/no). Values will be taken for all scorable teeth at six sites per tooth (mesio-buccal, mid-buccal, disto-buccal, mesio-lingual, mid-lingual and disto-lingual). No radiographs will be taken. The result of the periodontal treatment will be assessed on the healing response in the tissues using PPD, CAL, BOP, and the amount of inflamed periodontal tissue (PISA)[14].

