### Statistical methods

Sample size calculation was based on detecting a difference of 0.5% in HbA1c change from baseline between the two groups. Assuming a standard deviation of 1.0% and using a 2-sided test at 5% significance level, 64 participants per group would yield 80% power. Anticipating a 15% dropout rate, the target sample size was thus planned at 150 participants.

Baseline characteristics by group will be presented as mean (SD) for continuous variables and tallied for categorical variables. The intention-to-treat population will consist of all randomized subjects whereas the evaluable population will consist of subjects from the intention-to-treat population who complete the 3-months follow-up. Descriptive statistics will be provided for the intention-to-treat population.

All primary analyses will be performed according to intention-to-treat principles, on the evaluable population (i.e. all patients with initial (V1) and final (V4) HbA1c measurements), regardless of the subject's presence at intermediate visits or his/her degree of compliance with the treatment. Subjects with missing initial or final HbA1c measurements will be excluded from the analysis. The main analysis will be a comparison between the two study groups concerning the change in the HbA1c levels from baseline to 3 months in an analysis of covariance (ANCOVA) model, adjusted for the baseline HbA1c level and clinical centre. Residual values will be examined for an approximate normal distribution. If HbA1c values are highly skewed, a transformation or non-parametric method will be used instead [15].

The data will also be analysed using the "per protocol" approach. Here the analysis will be restricted to participants who were compliant with the treatment protocol (SRP, ATB and OHI).

In addition to the primary analysis, five binary outcomes for HbA1c at 3 months (a relative decrease of ≥10%, a three-month level of < 7%, an absolute decrease of ≥0.5%, a relative increase of ≥10% and an absolute increase of ≥0.5%) will be evaluated in logistic regression models adjusted for the baseline HbA1c level and clinical centre [16].

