For secondary outcomes, all continuous variables will be analysed via analysis of covariance using a model similar to that specified for the primary outcome. Analyses of binary variables will be based on logistic regression models adjusted for group and clinical centre. For secondary analyses, missing values will be imputed using the Last Observation Carried Forward method. The safety and efficacy of periodontal treatment will be assessed [17], as will the correlation between clinical response to periodontal treatment and HbA1c levels [18]. The proportion of subjects who had one or more adverse events in the two groups will be compared by means of Fisher's exact test.

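### The model for binary secondary variables leaves out the V1 value, which costs some power that data already collected could recover

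*Protocol article*

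**What the plan says.** All of the model statements are in *Statistical methods* of the protocol article.

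- **Primary outcome:** ANCOVA of the HbA1c change, with baseline HbA1c and centre as covariates.
- **Five binary HbA1c outcomes:** these "will be evaluated in logistic regression models adjusted for the baseline HbA1c level and clinical centre".
- **Continuous secondary variables:** "all continuous variables will be analysed via analysis of covariance using a model similar to that specified for the primary outcome", hence with a baseline term.
- **Binary variables in the secondary analyses:** "Analyses of binary variables will be based on logistic regression models adjusted for group and clinical centre".

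Under *Periodontal status*, bleeding on probing (BOP) is scored yes/no. On timing: "A full-mouth periodontal examination will be performed by trained dentists-examiners at V1 and V4 for both groups". On extent: "Values will be taken for all scorable teeth at six sites per tooth". On use: "The result of the periodontal treatment will be assessed on the healing response in the tissues using PPD, CAL, BOP", together with the inflamed surface area (PISA).

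Under *Outcomes*, the secondary outcomes named are fructosamine and SF-36 quality of life. Both are continuous. BOP is not among them.

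**The concern.** Three of the four model statements adjust for the baseline value and the fourth does not. The wording of the fourth is also odd: group is the effect being tested, not an adjustment, and it stands where the HbA1c sentence has the baseline term. That may be a slip, but nothing in the document shows it.

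This is a model that the article states, not a detail left for elsewhere. For any yes/no variable examined at both V1 and V4, the stated model ignores a covariate that the trial already holds and that usually predicts the outcome. What is at stake is power and the size of the reported odds ratio in supporting analyses, among them possibly the assessment of whether the periodontal treatment worked. The trial's main conclusion is not at stake.

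**Working it through.** **The plan's own figure.** The article gives no figure for binary secondary analyses, so the 64 per group from the HbA1c calculation is used here. It reproduces. For a difference of 0.5 and an SD of 1.0, two-sided 5%, 80% power, the normal approximation 2 × (1.96 + 0.84)² × 1.0² / 0.5² gives 62.8, so 63. The t-test solution is 63.8, so 64, with power 80.1% at 64. With 15% dropout, 128 / 0.85 = 150.6, against the planned 150.

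**Effect of leaving out V1.** Inputs:

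- From the document: 64 per arm, two-sided 5% level, group and centre in the model.
- Assumed, because the document gives none: a latent treatment effect of 0.6 SD, latent V1-V4 correlation ρ of 0.3, 0.5 or 0.7, and no centre effect.

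The latent V4 value is ρ × V1 + √(1 − ρ²) × noise + 0.6 × group, cut so that 50% of controls are positive. V1 is cut at the same point. Power over 6,000 simulated trials:

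| ρ | group + centre | + binary V1 | + continuous V1 |
|---|---|---|---|
| 0.3 | 75% | 76% | 77% |
| 0.5 | 76% | 80% | 82% |
| 0.7 | 75% | 84% | 88% |

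A separate run (3,000 trials, same latent effect, about 38% of controls positive) gave 78% to 79%, 77% to 82% and 76% to 86% with a binary V1 value, and 80%, 83% and 90% with a continuous one. Across both runs a binary V1 value adds from about 1 point at ρ = 0.3 to about 10 at ρ = 0.7.

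**Where the loss comes from.** In the table's setting the log odds ratio averages about 1.00 without V1. It is 1.05, 1.15 and 1.32 with a binary V1 value, and 1.07, 1.22 and 1.51 with a continuous one. The standard error is smaller without V1 (0.38, against 0.40 to 0.46 and 0.40 to 0.50). So the omission does not widen the interval. It moves the odds ratio towards 1 by more than it shrinks the standard error.

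**Validity.** With no treatment effect and ρ = 0.5, the stated model rejected in 4.7% of 6,000 trials, which is consistent with the nominal 5%.

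**Near-universal positivity.** Suppose 95% of controls are positive (assumed) and treatment lowers the latent value by 0.6 SD. Power is then only about 40%. A binary V1 value adds about 1 point at ρ = 0.3 or 0.5 and about 3 at ρ = 0.7. Trials in which the V1 term could not be estimated kept the unadjusted result, and about 4% with no usable fit were left out.

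**BOP by site, a conditional calculation.** *Pre-inclusion criteria (V0)* requires that patients "have at least six natural permanent teeth", so six teeth give 6 × 6 = 36 sites if all are scorable. If sites were modelled as independent, the design effect is 1 + (m − 1) × ICC, the standard error is too small by its square root, and the type I error is 2 × (1 − Φ(1.96 / √DEFF)). The ICC and the 20 teeth are assumed.

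| Sites m | ICC | DEFF | SE factor | Type I error |
|---|---|---|---|---|
| 36 | 0.05 | 2.75 | 1.7 | 24% |
| 36 | 0.10 | 4.5 | 2.1 | 36% |
| 120 | 0.05 | 6.95 | 2.6 | 46% |
| 120 | 0.10 | 12.9 | 3.6 | 59% |
| 1 (patient summary) | any | 1 | 1 | 5% |

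**The case against.** The strongest reply is about scope. The sentence belongs to a paragraph on secondary outcomes, and the two that are named are continuous, so no named outcome is governed by it. BOP is listed as an assessment, periodontal efficacy has a sentence of its own, and adverse events go to Fisher's exact test. All of this is correct, and it limits the weight of the point. It does not remove it, because the rule is stated for binary variables in general and its covariate set is weaker than those beside it.

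Second, omitting baseline in a randomised comparison is not an error, and a rule written for five HbA1c outcomes need not carry over to other variables. This also stands: the two rules differ, but they do not contradict each other.

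Third, a reader might infer that BOP will be analysed site by site as if sites were independent patients, with type I error of 24% or more. The documents do not support that. They say how a site is scored at examination, not what the unit of analysis is, and an article commonly leaves that to the full protocol. A percentage of bleeding sites per patient is continuous and would already fall under the baseline-adjusted ANCOVA. The planned correlation of clinical response with HbA1c, which has one value per patient, also points to patient-level summaries.

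**Conclusion.** The point holds for the missing V1 value, as a minor and inexpensive improvement to a stated model. The stated analysis keeps its type I error. Under the assumptions above it gives up about 1 to 10 points of power relative to a binary V1 covariate at moderate prevalence, and slightly more relative to a continuous one. The loss is close to nil for a binary covariate when almost all patients are positive. The figures depend on the assumed 0.6 SD effect and on correlations of 0.3 to 0.7, none of which the document supplies.

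Two stronger readings should not be drawn. The omission does not make the intervals wider, because the loss is in power and in an odds ratio nearer to 1. Inflated type I error for BOP is a risk only if sites are modelled without allowance for clustering, which the article does not say. The primary outcome, fructosamine, quality of life and the sample size are untouched.

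**What to change.** Replace the sentence on binary variables with:

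> Binary secondary variables will be analysed by logistic regression with treatment group, the V1 value of the variable (the underlying continuous V1 measure where one exists) and clinical centre.

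As a clarification, add:

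> BOP will be summarised for each patient as the percentage of bleeding sites and analysed by the baseline-adjusted ANCOVA.

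The cost is two sentences and no new data, since the periodontal examination is already done at V1 and V4. One consequence should be noted when results are reported: the odds ratio becomes conditional on the V1 value, so it is expected to be further from 1 than an unadjusted odds ratio and the two should not be compared directly.

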### Ethical aspects

All participants will have to provide written informed consent. The informed consent form will contain the following information: names and affiliations of investigators, a plain language description of the study (treatment group, control group and intervention), the duration of the study, the right to withdraw at any time, the ethics committee approval and the privacy guarantee. All participants will receive free periodontal treatment (immediate or delayed).

The protocol and procedures have been approved by ethics and regulatory agencies and are implemented in accordance with provisions of the Declaration of Helsinki and French Good Clinical Practice guidelines for periodontal treatment in diabetic patients. The appropriate Committee for Protection of Research Subjects (Comité de Protection des Personnes [CPP], Sud-Ouest Outre-Mer I), approved the protocol on February 23rd, 2009. The Sanitary Safety of Health Products Agency (Agence française de sécurité sanitaire des produits de santé [AFSSAPS]), approved it on February 12th, 2009 (ref: 2008-A01467-48). The Advisory Committee for Data Processing in Health Research (Comité consultatif sur le traitement de l'information en matière de recherche dans le domaine de la santé [CCTIRS]), gave its approval on January 15th, 2009.

## Discussion

We aim to use a two-centre, randomized, controlled trial to investigate whether periodontal treatment could lead to an improvement in glycaemic control in metabolically unbalanced diabetic patients suffering from periodontitis. The results of this trial will help to provide evidence-based recommendations for clinicians and a draft framework for designing local and national health policies.

## Abbreviations

ATB: systemic antibiotherapy; BOP: bleeding on probing; CAL: clinical attachment level; HbA1c: glycated hemoglobin; OHI: oral health instructions; PISA: periodontal inflamed surface area; PPD: periodontal pocket depth; SRP: scaling and root planing.
